### Home visits and WASH

On the day of inclusion (or as close as possible to inclusion date), staff/s will follow each caregiver home and will map the GPS coordinates of the house. At the first home visit, trained study staff will make an assessment of water sanitation and hygiene (WASH) characteristics and record this in the CRF. The WASH assessment is further described in the related SOP. Home visits are necessary to ensure that information is collected in a timely manner from participants who miss study clinic visits. Home visits will be carried out by well-trained study staff.

### Phone follow-up

Phone follow-up will be attempted in order to encourage caregiver attendance at designated appointment times as well as to gather basic health and compliance information during the study period. See section 22.9 for more information.

# Study setting and participants

## Study setting

The study is based in the districts of Jinja and Mayuge in the Busoga sub-region, Eastern Uganda. Here, the prevalence of child stunting is 29 percent, and although high, this is similar to the national average in Uganda [5]. The study clinics are set up at local community health centers. Local health centers are a keystone in providing healthcare access to children living in both rural and urban communities. This study will be incorporated into the community health center framework and will train local staff where possible. Appendix 1 provides a list of eight community health centers for which an agreement has been reached with the district health officer in order that study clinic operations may be carried out at those locations. Recruitment will begin at two health centers in the district of Jinja. Activities will expand to other clinics only if participant recruitment is slow. The study office is based in Jinja.

## Study participants

Seven hundred and fifty (N=750) children aged 12 to 59 months with a height-for-age z-score of less than -2 who meet the eligibility criteria will be invited to participate in the study.

## Eligibility criteria

### Inclusion criteria

- Aged 12 - 59 months.
- HAZ <-2 (WHO growth standards).
- Care-taker able and willing to return for follow-up visits, an initial home visit and agrees to phone follow-up.
- Living within the catchment area.
- Written informed consent given by parent/caregiver.

### Exclusion criteria

- SAM; measured as MUAC < 115mm OR weight-for-height z-score < -3 OR bilateral pitting oedema
- Medical complications requiring hospitalization.
- Obvious disability that impedes eating capacity.
- Disability that makes length/height assessment problematic
- Participation in another study or program which impacts on this study or previously enrolled in this study.
- Family plans to move away from the catchment area in the next 6 months.
- History or known allergy to peanuts or milk.

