### Screening

Screening is carried out at the study site. All children screened are allocated a screening ID number. Study staff who are trained in taking anthropometrics will measure the child’s MUAC, weight, height/length and check for oedema. If the child is classified as being stunted without SAM, qualified clinical study staff will assess the child according to the remaining inclusion and exclusion criteria. If all criteria are met, the caregiver is taken through the informed consent process. If informed consent is given, the child is included in the study.

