### Baseline measurements

Following inclusion, baseline measurements are taken according to the relevant SOPs. An example of the site flow at baseline is provided in figure 3. The following measurements are taken/assessed at baseline: questionnaires of medical history, demographics and dietary information, clinical assessment is conducted, blood and stool samples are collected, anthropometrics of the mother (if available) and child are measured, bioimpedance and child development assessed. A full description of the data collected at baseline is provided in section 22.

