### Random allocation

Thereafter, caregivers are informed of allocation to supplementation or the reference group. Those not allocated to supplementation are given a token of appreciation (given at each follow-up clinic visit), valued at around 5000 UGX but not more than 10 000UGX, for example clothes soap. If allocated to LNS caregivers are given training concerning appropriate use of LNS before they are allocated a two week supply. Prior to departure all caregivers are given a follow-up plan. Refer to the SOP for further details.

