## LNS-LQ nutrition composition

| **Table 1**: The nutritional composition of the four lipid-based nutrient supplements (LNS-LQ) | | | | | |
| --- | --- | --- | --- | --- | --- |
|  | Name | **Milk protein and whey permeate**  **LNS-LQ** | **Milk protein and no whey permeate**  **LNS-LQ** | **Soy protein and whey permeate LNS-LQ** | **Soy protein and no whey permeate**  **LNS-LQ** |
| Macronutrients | | | | | |
| Components | Unit | Per 100g | | | |
| Calories | Kcal | 531 | 535 | 530 | 534 |
| Carbohydrates | g | 42 | 43 | 42 | 43 |
| Lactose | g | 15.7 | 0.4 | 15.3 | 0 |
| Proteins | g | 13.9 | 13.5 | 13.9 | 13.5 |
| Milk proteins | g | 7.15 | 6.75 | 0.40 | 0 |
| Vegetable proteins | g | 6.75 | 6.75 | 13.50 | 13.50 |
| Lipids | g | 33.7 | | | |
| Linoleic acid C18:2 | g | 3.0 | | | |
| Alpha-linolenic acid C18:3 | g | 0.5 | | | |
| Minerals | | | | | |
| Calcium | mg | 691 | 594 | 691 | 594 |
| Copper | mg | 1.65 | | | |
| Iron | mg | 12 | | | |
| Iodine | µg | 127 | 113 | 127 | 113 |
| Magnesium | mg | 199.2 | 175.8 | 199.2 | 175.8 |
| Manganese | mg | 1.8 | | | |
| Phosphorus | mg | 661 | 539 | 661 | 539 |
| Potassium | mg | 1315 | 985 | 1315 | 985 |
| Sodium | mg | 84 | 7 | 156 | 79 |
| Selenium | µg | 30 | | | |
| Zinc | mg | 12.5 | | | |
| Vitamins | | | | | |
| Vitamin A | mg | 619 | | | |
| Vitamin B1 | mg | 1.2 | 1.1 | 1.2 | 1.1 |
| Vitamin B12 | µg | 3.2 | 3.0 | 3.2 | 3.0 |
| Vitamin B2 | mg | 3.1 | 2.8 | 2.7 | 2.4 |
| Niacin | mg | 14.9 | 14.6 | 14.9 | 14.6 |
| Pantothenic acid | mg | 5.7 | 4.5 | 5.7 | 4.5 |
| Vitamin B6 | mg | 2.1 | 2.0 | 2.1 | 2.0 |
| Biotin | µg | 74.1 | 67.6 | 74.1 | 67.6 |
| Folic acid | µg | 223 | | | |
| Vitamin C | mg | 67.9 | 67.6 | 67.9 | 67.6 |
| Vitamin D | µg | 16.9 | | | |
| Vitamin E | mg | 18 | | | |
| Vitamin K | µg | 30 | | | |

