## Blinding

This is a double blinded study. Both the study staff and the caregivers are blinded to which intervention is allocated to the study participant. Products are designed to be as indistinguishable as possible. The reference group is aware that they are not allocated to an intervention, however, the clinical study staff will not be made aware of which group participants are allocated to.

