# Ethics and dissemination

## Assessment of anticipated benefits and risks

Clinical benefits: It is anticipated that all children participating in this study will benefit from having close monitoring from doctors and study staff.

Community benefits: It is anticipated that the training of VHTs and clinical staff within the community will build capacity and enhance their awareness of the monitoring for child malnutrition, encouraging the practice at community clinic sites in the future.

Study risks: Deterioration to SAM. There is a very low-risk for deterioration to SAM. Such deterioration would likely be associated with another factor such as HIV or severe acute illness which are likely to be few in this population group.

Product risks: The intervention products are not expected to pose any risk to study participants. The only possible risk scenario would be if the child had an unknown allergy to an ingredient. This however is unlikely since serious allergies to peanuts or milk would likely already have been discovered prior to joining the study. There is a very low-risk for excessive weight gain (>2 WHZ) when assigned to an LNS-LQ product. If this occurs, we expect it to be in few cases who may take on weight first before linear growth is achieved. We do not expect this to have any negative long term consequences.

Procedural risks: There are very few procedural risks in this study. Blood samples are collected by trained nurses at two time points (at 0 and 12 weeks). Some temporary discomfort is experienced by the child when blood samples are taken but no other risk is expected.

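### The allergy exclusion names peanuts and milk but not soy, although soy protein isolate defines two of the four supplements

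*Protocol*

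**What the plan says.** The list of exclusions appears twice, in the Summary of protocol and under Exclusion criteria in the eligibility section. In both places the allergy item is "History or known allergy to peanuts or milk".

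The Screening section makes the listed criteria decisive: "If all criteria are met, the caregiver is taken through the informed consent process". A child whose caregiver then consents is included. Baseline work follows, including "questionnaires of medical history, demographics and dietary information, clinical assessment is conducted". Allocation comes after that: "Thereafter, caregivers are informed of allocation to supplementation or the reference group".

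The factorial design sets milk protein isolate (A and B) against soy protein isolate (C and D). Table 1 heads the column for product C "Soy protein and whey permeate LNS-LQ", and product D is the soy version without whey permeate. On blinding, the protocol states "Both the study staff and the caregivers are blinded to which intervention is allocated to the study participant".

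Under Assessment of anticipated benefits and risks, the product-risk paragraph says "The only possible risk scenario would be if the child had an unknown allergy to an ingredient". It calls this unlikely because "serious allergies to peanuts or milk would likely already have been discovered prior to joining the study".

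**The concern.** The protocol accepts the principle that a known allergy to something in the supplements is a reason not to enrol. It applies that principle to milk but not to the protein used as the alternative to milk. A caregiver may know that a child reacts to soy, and the child still passes every written criterion.

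Blinding removes an informal safeguard. The products are made to look and taste as alike as possible, and caregivers and clinical staff do not know which one a child has. The distributors see a product code but not its meaning, and the codes stay locked until after the primary analysis. A caregiver who avoids soy at home could not recognise a soy sachet.

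The risk text has the same gap. It treats unknown allergy as the whole of the product risk, which would follow if every relevant known allergy were excluded. For soy that is not so.

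**Working it through.** There is no figure in the protocol to reproduce. The check is a reading of the criteria against the products, with simple arithmetic for size.

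**1. Does any other criterion catch a known soy allergy?** The remaining inclusion and exclusion items concern:
- age and height-for-age;
- willingness to attend and be phoned, living in the catchment area, and plans to move away;
- consent;
- severe acute malnutrition, and complications needing hospital care;
- disability affecting eating or length measurement;
- participation in other studies, or earlier enrolment in this one.

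None covers soy. There is no clause on allergy to any ingredient, and no exclusion at the investigator's discretion.

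**2. Is soy a main ingredient?** Table 1, per 100 g sachet:

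| Product | Protein type | Milk protein (g) | Vegetable protein (g) |
| --- | --- | --- | --- |
| A | milk, with whey permeate | 7.15 | 6.75 |
| B | milk, no whey permeate | 6.75 | 6.75 |
| C | soy, with whey permeate | 0.40 | 13.50 |
| D | soy, no whey permeate | 0 | 13.50 |

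C and D carry 13.50 − 6.75 = 6.75 g more vegetable protein per sachet than A and B. That equals the 6.75 g of milk protein that D lacks compared with B. At one sachet a day for 12 weeks this is 12 × 7 = 84 sachets. The source of the 6.75 g of vegetable protein in A and B is not stated, so soy exposure there can be neither assumed nor ruled out. The point does not depend on it.

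**3. How many children receive a soy product?** Each arm has 150 children.
- C + D = 150 + 150 = 300.
- Share of all children: 300/750 = 40%.
- Share of supplemented children: 300/600 = 50%.

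For comparison, milk protein is in A, B and C, so 450/750 = 60% of children receive some, and known milk allergy is excluded.

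**4. How many might be affected?** The protocol gives no prevalence of known soy allergy. Let *p* be that prevalence among otherwise eligible children, and assume *p* between 0.0001 and 0.005.
- Expected in C and D: 300 × 0.0001 = 0.03, up to 300 × 0.005 = 1.5.
- Expected among all 750: 750 × 0.0001 = 0.075, up to 750 × 0.005 = 3.75.

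One affected child would be expected in C and D at *p* = 1/300, or about 0.33%, so most of the assumed range gives fewer than one.

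**5. Does the risk text hold?** It holds for peanuts and milk, where known allergy is excluded and only unknown allergy is left. For soy, known allergy is left as well.

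**The case against.** The strongest reply is that the practical effect is close to nil.

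- **Rarity.** Known soy allergy may be very rare in this population, and nothing in the protocol suggests it is a recognised problem there. The range used above is an assumption. The 40% is the share of children given soy, not the share at risk. This stands, and it keeps the point minor. Yet the protocol also calls serious undiscovered peanut or milk allergy unlikely, and it still lists both allergies as exclusions.
- **Other chances to catch the child.** Medical history, dietary questions and clinical assessment come before the first sachet, and the investigator may discontinue a child at any time in the child's interest. This also stands: a reported allergy could be acted on before exposure. But no part of the protocol requires anyone to ask about soy, and discontinuing an enrolled child is no substitute for an eligibility rule.
- **Material not seen.** The screening procedures, case report form and consent material are not available here. If caregivers are told that any product may contain soy, one who knows of an allergy could decline without knowing the product code. That limits the conclusion to the written criteria. The criteria themselves belong in the protocol.
- **The risk wording is generic.** Unknown allergy to an ingredient includes soy, so the paragraph can be read as incomplete rather than contradictory. This is a fair reading. The weakness follows from the same omission and is not a separate error.

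**Conclusion.** The concern holds as a minor patient-safety gap. As written, the criteria admit a child with a known soy allergy, and such a child, once randomised, has a 40% chance of being allocated a product built on soy protein isolate, under blinding. The reassurance about product risk does not hold for soy.

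Confidence is high about the wording and low about how many children it would ever affect. That number rests wholly on an assumed prevalence. It also takes no account of the chance that the baseline history or the consent discussion would identify the child first. No effect on bias, power or sample size is claimed.

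**What to change.** Add soy as a third named allergen in the exclusion item, in both the Summary of protocol and the Exclusion criteria. Make the same addition to the sentence on peanuts and milk under Assessment of anticipated benefits and risks.

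The text change is one word in each of three places. Because it bears on participant safety, it may count as a substantial amendment under the protocol's own definition and so need ethics approval first. Screening forms and procedures may need the same update.

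The cost in recruitment is about 0.075 to 3.75 children per 750 under the assumed prevalence. They would be turned away before randomisation, so the design, the target of 750 and the analysis are unaffected.

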# Intervention

This is a community-based supplementary food intervention.

## Description of LNS-LQ investigational products

In this study, four different LNS-LQ formulations are used to supplement the diet of stunted children. The supplements are composed in a two by two factorial design, varying with respect to the incorporation of milk based ingredients; whey permeate and milk protein isolate. These supplements are standardized to contain similar proportions of energy, protein and carbohydrates. Each formulation contains a mineral and vitamin mix to improve micronutrient intake, the milk minerals provided by the whey permeate in two of the supplements are in addition to the standard amount provided. In as much as is possible, the supplements are designed to have a similar appearance, texture, colour and taste. Table 1 provides an overview of the LNS interventional product compositions.

## Rationale for use of LNS-LQ

LNS is a nutrient dense fortified lipid-based paste that is produced to meet high quality and safety standards. It is well adapted for use in homes where few resources are available, for example; LNS has a long shelf life, is packaged in daily portion sizes, does not require refrigeration, does not require preparation, mixing or diluting and can be consumed directly from the sachet.

## Dosage

Children randomised to LNS will be allocated one 100g sachet of LNS-LQ (530-535kcal) per day for 12 weeks.

## Rationale for dosage

The energy need per kg body weight for healthy 1-5 year-old children is around 100 kcal/kg/day with slightly higher needs at 1 year decreasing with age (<http://www.fao.org/3/aa040e/AA040E07.htm>). To provide enough nutrients for catch-up growth, the formulation has been designed/selected to meet up to 50% of the total energy requirements and 100% of micronutrients needs [26]. In addition, the dose of milk protein and whey permeate in the LNS-LQ corresponds to approximately 20-25 g milk powder or 1 glass of milk per day, which has been associated with increased linear growth in other studies [27]. We do not foresee a risk of overweight. In one of our previous studies, short children with low MUAC aged 6 – 23 months gained mainly fat-free mass and not excessive fat mass after intake of a similar dose of energy and nutrients [28]For treatment of children aged 12-59 months with MAM, it is recommended to provide 75 kcal/kg body weight, approximately half of the daily energy requirements (to supplement the family diet) and enough micronutrients to cover all of the child’s daily requirements . Children with MAM measuring between 65 and 87cm can weigh between 5.5 and 10.4 kg , and therefore require a daily supplement of between 413 kcal (5.5 kg * 75 kcal/kg) and 780 kcal (10.4 kg * 75 kcal/kg). Our dose of 540kcal is in line with the current WFP (510-560kcal/100g) and USDA (520-550kcal/100g) recommendations for daily supplementation of MAM.

## Administration of study treatment

At inclusion, clear instruction is given to the caregiver on how to safely and correctly give the supplement to the participating child in the home. These messages are reinforced throughout the duration of supplementation. The SOP describes the messages being communicated.

## LNS-LQ nutrition composition

| **Table 1**: The nutritional composition of the four lipid-based nutrient supplements (LNS-LQ) | | | | | |
| --- | --- | --- | --- | --- | --- |
|  | Name | **Milk protein and whey permeate**  **LNS-LQ** | **Milk protein and no whey permeate**  **LNS-LQ** | **Soy protein and whey permeate LNS-LQ** | **Soy protein and no whey permeate**  **LNS-LQ** |
| Macronutrients | | | | | |
| Components | Unit | Per 100g | | | |
| Calories | Kcal | 531 | 535 | 530 | 534 |
| Carbohydrates | g | 42 | 43 | 42 | 43 |
| Lactose | g | 15.7 | 0.4 | 15.3 | 0 |
| Proteins | g | 13.9 | 13.5 | 13.9 | 13.5 |
| Milk proteins | g | 7.15 | 6.75 | 0.40 | 0 |
| Vegetable proteins | g | 6.75 | 6.75 | 13.50 | 13.50 |
| Lipids | g | 33.7 | | | |
| Linoleic acid C18:2 | g | 3.0 | | | |
| Alpha-linolenic acid C18:3 | g | 0.5 | | | |
| Minerals | | | | | |
| Calcium | mg | 691 | 594 | 691 | 594 |
| Copper | mg | 1.65 | | | |
| Iron | mg | 12 | | | |
| Iodine | µg | 127 | 113 | 127 | 113 |
| Magnesium | mg | 199.2 | 175.8 | 199.2 | 175.8 |
| Manganese | mg | 1.8 | | | |
| Phosphorus | mg | 661 | 539 | 661 | 539 |
| Potassium | mg | 1315 | 985 | 1315 | 985 |
| Sodium | mg | 84 | 7 | 156 | 79 |
| Selenium | µg | 30 | | | |
| Zinc | mg | 12.5 | | | |
| Vitamins | | | | | |
| Vitamin A | mg | 619 | | | |
| Vitamin B1 | mg | 1.2 | 1.1 | 1.2 | 1.1 |
| Vitamin B12 | µg | 3.2 | 3.0 | 3.2 | 3.0 |
| Vitamin B2 | mg | 3.1 | 2.8 | 2.7 | 2.4 |
| Niacin | mg | 14.9 | 14.6 | 14.9 | 14.6 |
| Pantothenic acid | mg | 5.7 | 4.5 | 5.7 | 4.5 |
| Vitamin B6 | mg | 2.1 | 2.0 | 2.1 | 2.0 |
| Biotin | µg | 74.1 | 67.6 | 74.1 | 67.6 |
| Folic acid | µg | 223 | | | |
| Vitamin C | mg | 67.9 | 67.6 | 67.9 | 67.6 |
| Vitamin D | µg | 16.9 | | | |
| Vitamin E | mg | 18 | | | |
| Vitamin K | µg | 30 | | | |

# Reference group

This study includes a group of 150 un-supplemented stunted children as a reference group. These children will not receive an intervention product, but instead will continue with the family diet and will receive locally adapted nutrition counselling as well as monitoring and regular follow-up over the intervention period.

# Deterioration and referral

Children identified as having SAM (MUAC < 115 mm OR WHZ <-3 OR bipedal pitting oedema) prior to inclusion, or participants in the study who deteriorate to SAM (without other complications) are referred for outpatient treatment of SAM (OTC). If the child also has complications, they are referred to inpatient care (ITC). Those identified as having MAM but who are younger than the recruitment age, will be referred to local NGO services or other health facilities for caregiver nutritional/social support (where available). All participants requiring hospital attention will be referred for treatment and attempts will still be made to follow-up on the child wherever possible.

# Concomitant care for study participants

Participants will not be provided with any medical treatment by the study. Wherever treatment is needed, children are referred for the necessary medical attention.

# Strategies to improve and monitor adherence

It is a challenge to ensure that the participating child is the one receiving the LNS, due to home based caregiver administration. As such, several actions are taken to improve compliance.

- Siblings: We aim to only include one child per household in the study. However, if there are other young children in the household (6 months to five years), instructions and sachets will be given so that the caregiver receives extra rationing. This strategy aims to minimize the likelihood of sharing.
- Identification: Several methods are used to ensure that the correct child is matched to the correct study records, namely wrist bands and photo id. The SOP describes the use of these processes in detail.
- Accountability: Any distribution of sachet stocks will be logged by study staff. Additionally, when collecting new sachets, the caregiver is requested to return the empty sachets from their previous two week supply. This is to improve accountability on the part off the caregivers, and encourage against sachet redistribution or selling.
- Monitoring adherence: Trained study staff will make regular phone follow-up calls to the participant/caretakers to remind them of their clinic visits and enquire about stool sample collection or LNS adherence where applicable. At clinic visits and when the caregiver is collecting sachet stocks study staff will also enquire about LNS adherence.
- Incentives: Throughout the study, the child’s health will be monitored regularly. A travel reimbursement of not more than 20,000UGX will be provided to cover the cost of return transport and includes some allowance for e.g. food purchase during the day while at the clinic visit. Any caregivers attending with unsupplemented children will also receive a small token which can be appreciated by the whole family, for example clothes soap. The value will not exceed 10,000UGX.

